## Abstract

**Background:**

Increasing attention is being given to the growing concerns about social isolation, loneliness, and compromised emotional well-being experienced by young adults and older individuals affected by Alzheimer disease and related dementias (ADRD). Studies suggest that reminiscence strategies combined with an intergenerational approach may yield significant social and mental health benefits for participants. Experts also recommended the production of a digital life story book as part of reminiscence. Reminiscence is typically implemented by trained professionals (eg, social workers and nurses); however, there has been growing interest in using trained volunteers owing to staffing shortages and the costs associated with reminiscence programs.

**Objective:**

The proposed study will develop and test how reminiscence offered by trained young adult volunteers using a digital storytelling platform may help older adults with ADRD to improve their social and emotional well-being.

**Methods:**

The proposed project will conduct a randomized controlled trial to assess the effects of the intervention. The older and young adult participants will be randomly assigned to the intervention (reminiscence based) or control groups and then be randomly matched within each group. Data will be collected at baseline before the intervention, in the middle of the intervention, at end of the intervention, and at 3 months after the intervention. An explanatory sequential mixed methods design will be used to take advantage of the strengths of both quantitative and qualitative methods. The quantitative data from surveys will be entered into SPSS and analyzed using covariate-adjusted linear mixed models for repeated measures to compare the intervention and control groups over time on the major outcomes of participants. Conventional content analysis of qualitative interviews will be conducted using data analysis software.

**Results:**

The project was modified to a telephone-based intervention owing to the COVID-19 pandemic. Data collection started in 2020 and ended in 2022. In total, 103 dyads were matched at the beginning of the intervention. Of the 103 dyads, 90 (87.4%) dyads completed the midtest survey and 64 (62.1%) dyads completed the whole intervention and the posttest survey. Although we are still cleaning and finalizing data analyses, the preliminary results from both quantitative and qualitative data showed promising results of this intergenerational reminiscence approach that benefits both the older adults who have cognitive impairments and the young adult participants.

**Conclusions:**

Intergenerational reminiscence provided by young adult college student offers promising benefits for both the younger and older generations. Future studies may consider scaling up this pilot into a trackable, replicable model that includes more participants with diverse background (eg, public vs private college students and older adults from other agencies) to test the effectiveness of this intervention for older adults with ADRD.

**Trial Registration:**

ClinicalTrials.gov NCT05984732; https://classic.clinicaltrials.gov/ct2/show/NCT05984732

**International Registered Report Identifier (IRRID):**

DERR1-10.2196/49752

## Introduction

### Background

The projected number of individuals aged ≥65 years living with Alzheimer disease and related dementias (ADRD) is expected to reach 7.1 million by 2025, marking a 22% increase from the current figure of 5.8 million older adults affected [1]. Unless significant advancements in medical research lead to preventive measures, treatments, or cures for ADRD, these statistics are projected to escalate to 13.8 million by 2050 [1]. In addition to memory loss, difficulties in daily functioning, and behavioral symptoms, ADRD profoundly affects the social and emotional well-being of those living with the condition.

Most older adults with ADRD live in the community, and many of these individuals live alone [1,2]. There is growing concern about social isolation and loneliness among people with ADRD, particularly as both have been widely linked to poor physical health outcomes and compromised quality of life and well-being [3]. Studies suggest that people with ADRD are at great risk for social withdrawal, social isolation, and loneliness [4]. Individuals with ADRD also tend to have few close friends, which may negatively affect their quality of life [5]. In addition, ADRD is associated with increased risk of depression; anxiety; and other negative emotional well-being outcomes [6], including decreased resiliency, which may prevent individuals from recovering from life’s challenges [7,8]. Although there are no interventions to prevent or cure ADRD, there is a pressing need to address and understand the social and emotional well-being of people with the disease.

However, people of all ages may experience social isolation and loneliness. The younger generation has various sources that caused their loneliness. It has been reported that Generation Z (aged 18-22 years) is the loneliest generation and claims to be in worse health than older generations [9]. Overall, 7 out of 10 respondents feel alone (73%), shy (72%), or that no one really understands them well (71%) [9]. In the workplace, they also feel abandoned by their coworkers when under pressure at work (42%), alienated by their coworkers (40%), emotionally distant from the people they work with (54%), and disconnected from others at work (55%) [9]. Moreover, young adults were reported to experience heightened levels of loneliness and mental health challenges during the COVID-19 pandemic [10]. Neglecting the issue of social isolation and loneliness can have detrimental effects on both the mental and physical well-being of individuals, as evidenced by studies such as that by Mushtaq et al [11]. Therefore, it is crucial to develop programs or interventions that aim at preventing or addressing loneliness, so that physical and mental health of young and older adults is maintained.

### Reminiscence Approach

Reminiscence has been identified as a potentially effective intervention strategy for alleviating depression [12-14] and in promoting social and emotional well-being for older adults [15]. Reminiscence typically involves a discussion of past activities, events, and experiences aided by the use of familiar items and objects such as photographs and music [16]. Reminiscence work with people with ADRD is viewed as a psychosocial intervention with a credible evidence base [17]. There is also evidence suggesting that individual reminiscence work that involves a life review and subsequent production of a life story book is associated with improvements in the well-being of people with ADRD [18].

### Intergenerational Reminiscence Approach

Studies suggest that reminiscence combined with an intergenerational approach may yield significant social and mental health benefits for young and older adults. Through intergenerational reminiscence, older people may pass on their life experiences and life lessons to younger generations [19,20], and the sharing of autobiographical memories has both social and psychological functions [21]. Previous studies also assert that the use of an intergenerational approach is an effective strategy for promoting positive social and mental health in later life, such as reducing social isolation or loneliness [22]. Establishing intergenerational contact and fostering relationships between older individuals and young adults serve as effective measures to prevent the formation of stereotypes or negative attitudes and to challenge and dispel existing ones [23,24]. In addition, intergenerational programming can enable the younger generation to develop meaningful connections with older adults [23].

Reminiscence is typically implemented by trained professionals (eg, social workers and nurses); however, there has been growing interest in using trained volunteers owing to staffing shortages and the costs associated with reminiscence programs [25]. As part of the efforts to use volunteers rather than professionals, the concept of joining young volunteers and older generations together for intergenerational reminiscence has emerged as a promising area of research. So far, the work of Chung [25] and Gaggioli et al [26] are the only peer-reviewed studies implementing intergenerational reminiscence with young volunteers. Although several benefits were reported for both generations in these 2 studies, the small size of the sample and absence of a control condition limited the study results. The findings underscore the need for more studies related to intergenerational reminiscence that include young adult volunteers, as this approach may potentially offer a more sustainable and cost-effective intervention for implementation in community-based settings. Thus, more studies are needed to better understand and rigorously measure this approach to intergenerational reminiscence interventions, particularly for older adults with ADRD.

### Reminiscence and Digital Storytelling

There are previous studies of reminiscence work that endorse the use of a life story book that are pertinent to the proposed study [18,25]. Recent studies recommend the production of a digital life story book [17] as part of reminiscence. Digital storytelling (DST) is a technology that uses a 2- to 5-minute audio-visual clip combining text, images, music, photographs, voice-over narration, and other audio [27]. Psychological well-being benefits of DST for the general population have been reported in a systematic review [28]. Previous studies also demonstrate the benefits of DST for people with ADRD [29,30]. Studies of intergenerational DST, which combines DST and intergenerational programming, reported positive outcomes including reciprocal relationships, empathy, connection, and confronting agism [31]. However, few studies combined a reminiscence approach and DST or intergenerational DST. Thus, this study is the first one to develop and test how intergenerational reminiscence using a DST platform may help older adults with ADRD and young adults to improve their social and emotional well-being.

### College Student Involvement

The proposed study will include young adult volunteers recruited from University of Texas at Arlington (UTA), a large and diverse institution of higher education. The rationale for including undergraduate and graduate students in the proposed study is that the positive impact of intergenerational learning experiences on students’ academic and personal development is well documented [32]. Previous studies support the value of intergenerational activities in postsecondary education; provide evidence of benefits, reciprocity, and empowerment outcomes [33]; and suggest that these learning experiences may better prepare undergraduate and graduate students for future work with older adults [31]. Studies further suggest that intergenerational learning experiences that involve interactions with people with ADRD also result in positive gains in academic learning and attitude toward older adults among college students [34]. By connecting young adult volunteers with older adults through interactions during the proposed intervention and preintervention training, this proposed study aims to have a positive influence on attitudes toward aging and knowledge about ADRD. Furthermore, with rapidly changing demographics in the United States, there is an urgent need to combat the stereotypes and negative attitudes toward aging and agism and discrimination of older adults that often exists among younger populations [35].

Studies suggest that intergenerational reminiscence is promising for individuals with ADRD; however, these studies are limited by small sample sizes and less rigorous study designs. A recent systematic review of reminiscence therapy provided in the Cochrane Library specifically recommends large-scale, randomized controlled trials that include a life story book component for people with ADRD [17]. Although a few studies have attempted to use young volunteers as part of small-scale intergenerational reminiscence studies [25,26], the use of undergraduate and graduate students is unexamined so far.

### Aims and Research Questions

#### Overview

To fill the abovementioned research gaps, the proposed study aims to develop and evaluate the feasibility and effectiveness of an intergenerational reminiscence approach in improving the social and emotional well-being of older adults with ADRD. The intervention is guided by continuity theory [36], which posits that the reminiscence process guides individuals to adjust and adapt to changes that occur in their lives. Moreover, a continuity theory approach to reminiscence may also facilitate a strong sense of self [37] and has been recently used in other reminiscence interventions [38]. On the basis of literature and the continuity theory, it is hypothesized that the framework of reminiscence combined with an intergenerational approach and DST will help to improve the social and emotional well-being of both generations and help strengthen or build resilience in older adults with ADRD. Specifically, the study addresses 5 goals.

#### Goal 1—To Quantitatively Test the Effectiveness of This Intervention in Improving the Social Well-Being of Older Adults With ADRD and Young Adults

The objectives are to (1) provide a 10-session intervention with reminiscence and DST to older adults by trained young adult volunteers and (2) test whether older or young adults report significant improvement in quality of life or decline in loneliness after the intervention. Hypotheses include the following: (1) older participants in the intervention group will have high levels of quality of life in the middle of and after the intervention compared with their pretest scores and compared with those in the control group and (2) young and older participants in the intervention group will have low levels of loneliness in the middle of and after the intervention compared with their pretest scores and compared with those in the control group.

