#### Goal 2—To Quantitatively Test the Effectiveness of This Intervention in Improving the Emotional Well-Being of Older Adults With ADRD

The objectives are to (1) provide a 10-session intervention with reminiscence and DST to older adults by trained young adult volunteers and (2) test whether older adults report significant changes in affect or resilience after the intervention. Hypotheses include the following: (1) older participants in the intervention group will have high positive affect (PA) and low negative affect (NA) in the middle of and after the intervention compared with their pretest scores and compared with those in control group and (2) older participants in the intervention group will have high resilience scores in the middle of and after the intervention compared with their pretest scores and compared with those in control group.

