## Methods

### Study Design

The proposed project will conduct a randomized controlled trial to assess the effects of the intergenerational reminiscence approach with DST on the social and emotional well-being of older adults with ADRD. An explanatory sequential mixed methods design [39] will be used, which first involves collecting quantitative data and analyzing the data to identify subsamples of participants who report the greatest and least changes and then conducting qualitative interview with these subsamples. Half (46/92, 50%) of the dyad sample will receive the reminiscence DST intervention, and the other half (46/92, 50%) of the sample will receive a regular social visit from young adult volunteers without the intervention. Dyads will be randomly assigned to either the intervention or control group after baseline screening of all participants and, subsequently, randomly matched within each group. To further prevent selection bias, statistical techniques such as covariate-adjusted linear mixed models will be used to adjust for covariate imbalance during data analysis.

A total of 92 dyads are required to test the effectiveness of the intervention in this proposed study (refer to power analysis in the *Sample and Recruitment Plan* section). We will recruit participants on a rolling basis until we recruit 92 dyads. At least one-fourth (23/92, 25%) of the total sample of older adults and young adult volunteers will be recruited before they are randomly matched. Upon signing the consent form, participants will be given the chance to engage in the study. They will be provided with guidance throughout the informed consent process and will subsequently undergo a baseline survey in which all measures will be collected blind to group conditions.

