### Sampling and Recruitment Plan

Power analyses performed using G*Power 3.1.9 indicated that a total of 92 dyads (or 184 participants) are required to address our study objectives using a linear mixed model. This sample size estimate was based on a small effect size *(f*=0.22), a significance level of α=.05, β of .20, anticipated *r* over time of 0.30, and 5% attrition rate based on the findings of Chung [25], for 2-tailed tests.

Participants in this study will be community-dwelling older adults and undergraduate and graduate students (ie, young adult volunteers) enrolled at UTA. The eligibility criteria of the older adult participants include individuals who (1) are aged ≥65 years; (2) have cognitive impairment measured by the Ascertain Dementia 8 (AD8) [41]; (3) have decisional capacity as measured by the University of California, San Diego Brief Assessment of Capacity to Consent (UBACC) [42]; (4) are not participating in any other research protocol currently; and (5) can speak and understand English. The exclusion criteria for older adults are (1) participating in another trial, (2) having health issues that prevent them from participating in the study for 3 months, and (3) inability to commit to being available for the full 10 weeks of the intervention.

The older adult participants will be recruited through Tarrant County Meals On Wheels (MOW), which is a partner agency of the Area Agency on Aging of Tarrant County. Eligibility criteria to enroll in Tarrant County MOW is that a person must be homebound and have no one to help them on a regular basis. The Area Agency on Aging is very committed to expanding services and supports to people with ADRD, as many MOW clients with ADRD are living alone in Tarrant County. Moreover, studies suggest the need for additional research in the area of loneliness among clients using MOW [43]. Participant recruitment will begin with case managers and other MOW staff using their client database system to search for clients with ADRD who meet the study criteria. Next, case managers will contact potential study participants and then ask for permission to share their telephone number with a member of the UTA research team. The principal investigators (PIs) and graduate research assistants (GRAs) will follow-up with all the potential participants provided by MOW.

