## Results

The study was funded in January 2021. Data collection started in May 2021 and ended in mid-2022. In total, 103 dyads were matched at the beginning of the intervention. Of the 103 dyads, 90 (87.4%) dyads completed the midtest survey and 64 (62.1%) dyads completed the posttest survey. Although a total of 92 dyads were planned to test the effectiveness of the intervention in this proposed study, the post hoc power analyses performed using G*Power 3.1.9 indicated that 64 dyads will yield sufficient power to test the interaction between groups over time (power=0.95), the changes over time (power=0.95), and the differences between the groups (power=0.71). These parameters are based on a small anticipated effect size (*f*=0.22), α=0.05, two-tailed, with measures correlated at r=0.30.

We also collected qualitative interview data for this study with selected dyads in the intervention group (8/27, 30%). Weekly reflection page from UTA student participants, weekly fidelity check forms, final digital story books, and final scrapbooks were also saved for future data analyses. We are currently engaged in data cleaning and analysis for both quantitative and qualitative data. One manuscript has already been published [73], and we anticipate publishing several more manuscripts reporting the results within the next 1-2 years.

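### The power reported as sufficient at 64 dyads is not the power of the mid- and post-intervention comparisons with control that Goals 1 and 2 name

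*Protocol article*

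**What the plan says.** **Hypotheses.** Goal 1 predicts better quality of life and less loneliness "in the middle of and after the intervention compared with their pretest scores and compared with those in the control group". Goal 2 does the same for affect and resilience, for example "older participants in the intervention group will have high resilience scores in the middle of and after the intervention compared with their pretest scores", and adds the comparison with control. The testing objective under Goal 1 is looser: "test whether older or young adults report significant improvement in quality of life or decline in loneliness after the intervention".

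**Planned size.** Sampling and Recruitment Plan gives the requirement as follows: "a total of 92 dyads (or 184 participants) are required to address our study objectives using a linear mixed model". Its inputs are f=0.22, which it calls small, together with "a significance level of α=.05, β of .20, anticipated *r* over time of 0.30, and 5% attrition rate" and two-sided tests. It names neither the effect tested nor the number of surveys entered.

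**Achieved size.** Results reports 64 dyads at posttest and describes the power as sufficient on three figures: interaction 0.95, time 0.95 and "the differences between the groups (power=0.71"). All three are said to rest on f=0.22 and r=0.30.

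**Analysis.** Statistical Analysis plans a covariate-adjusted linear mixed model over four surveys. A significant interaction leads to post hoc tests, and there is no multiplicity adjustment.

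**The concern.** The hypotheses concern particular times: a difference from control at midpoint and a difference after the intervention. An arm difference averaged over all four surveys is another quantity. It includes baseline, where randomised arms have no treatment effect, and it gains precision from averaging that a comparison at one survey does not have.

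The interaction figure is closer in spirit, but f=0.22 on the interaction scale is not the same treatment effect as f=0.22 on the between-group scale. Quoting both under one small effect size makes the design look better powered than it is.

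The claim matters because it is used to reassure the reader after 103 matched dyads fell to 64 (39/103 = 37.9% lost, against a planned 5%). If the named comparisons have much lower power, a non-significant result could be misread as evidence of no effect.

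**Working it through.** **Inputs.** f=0.22, α=0.05 two-sided and r=0.30 (Sampling and Recruitment Plan; Results). Allocation: "Half (46/92, 50%) of the dyad sample will receive the reminiscence DST intervention", so 46 per arm at 92 dyads. For the 64 completing dyads I assume 32 per arm. There are four surveys. For two equal arms d=2f=0.44 SD. I also assume equal SDs and a correlation of 0.30 between every pair of surveys.

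**1. Reproducing the printed powers (N=64, m=4).**
- Between groups: λ = N·f²·m/(1+(m−1)r) = 64×0.0484×4/1.9 = 6.52 on 1 and 62 df; power 0.710 (printed 0.71).
- Time and interaction: λ = N·f²·m/(1−r) = 12.39/0.70 = 17.70 on 3 and 186 df; power 0.952 (printed 0.95).

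All three figures match.

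**2. What the 0.71 assumes.** Averaging four surveys cuts the error variance to (1+3×0.30)/4 = 0.475 of a single survey's. The 0.44 SD gap is the mean over all four surveys. With no baseline gap and an equal gap D at the three later surveys, that mean is 3D/4, so D = 0.44×4/3 = 0.587 SD.

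**3. What the 0.95 for the interaction assumes.** For gaps (0, D, D, D) the mean is 0.75D and the mean squared deviation is 0.1875D². Half of each deviation falls to each arm, so f = √0.1875/2 × D = 0.2165D. Setting f=0.22 gives D = 1.02 SD.

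The same printed f therefore stands for a later gap of 0.587 SD in one figure and 1.02 SD in the other.

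**4. Power with one pattern held fixed** (no baseline gap, equal gap D at each later survey):

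| Test | D=0.44, 64 dyads | D=0.44, 92 dyads | D=0.587, 64 dyads | D=0.587, 92 dyads |
|---|---|---|---|---|
| One survey, arm vs control | 0.41 | 0.55 | 0.64 | 0.80 |
| Average of four surveys | 0.47 | 0.62 | 0.71 | 0.86 |
| Interaction | 0.30 | 0.42 | 0.50 | 0.68 |

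The single-survey row is a two-sample t test with noncentrality D√(n/2): 0.44×√16 = 1.76 at 32 per arm and 0.44×√23 = 2.11 at 46 per arm. The average row comes from simulation (40,000 trials).

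Sensitivity of the single-survey figure at 0.44 SD:
- Baseline-adjusted: 0.44 (64 dyads) and 0.59 (92 dyads).
- Change from baseline: 0.31 and 0.42.
- If the 27 intervention dyads given in Results are the completers in that arm, 27 versus 37 gives 0.40.

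**5. Detectable difference.** At 32 per arm, 0.80 power for one survey needs D of about 0.71 SD.

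**6. The planned 92.** The between-group test with four surveys needs 79 dyads, or 84 after 5% attrition; at 92 its power is 0.857. With three surveys it needs 89, or 94 after attrition, and 88 analysed dyads give 0.798. The interaction with four surveys needs 41, or about 45 after attrition. So 92 fits a three-survey between-group test, not a four-survey one, and the article does not say which was used.

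**The case against.** Three points on the other side carry weight.

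**No joint rule is fixed.** A reader might infer that success requires significance at midpoint and after the intervention, against both pretest and control. The documents do not support that. The hypotheses describe an expected pattern, the Goal 1 objective speaks only of change after the intervention and links its outcomes with an or, and Statistical Analysis allows for partial patterns. If such a rule were read in, power to beat control at both times would be about 0.21 (64 dyads) to 0.35 (92) at 0.44 SD, or 0.45 to 0.66 at 0.587 SD. Adding both pretest comparisons would give 0.11 to 0.24, or 0.34 to 0.59. These figures illustrate a reading; they are not the trial's power.

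**Not every stated power is for an average.** Results also prints the interaction and time figures, and the interaction is what the analysis plan would follow up. That is correct, but the 0.95 does not rescue the claim: at 0.44 SD the interaction has power 0.30 at 64 dyads.

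**The shortfall depends on where f=0.22 is placed.** Held as the four-survey average, it leaves the single-survey contrast at about 0.80 with 92 dyads. That stands and is why both placements are shown. At 64 dyads the contrast is still only 0.64.

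The study also calls itself preliminary. That excuses modest power, but not describing it as sufficient.

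**Conclusion.** The point holds for the power statement. At 64 dyads the reported sufficiency does not apply to the comparisons with control that Goals 1 and 2 name: power for one survey is about 0.41 at 0.44 SD, or 0.64 at 0.587 SD, and 0.80 power needs about 0.71 SD. The printed 0.71 and the 0.95 for the interaction are correctly computed but imply different treatment effects.

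That the 0.71 is a four-survey average is firm, because it reproduces exactly. For the planned 92 dyads the test is unnamed and can only be inferred, so it would be wrong to say that the planned 0.80 is also a four-survey average.

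The sizes rest on equal correlations of 0.30, equal SDs, a 1:1 split of completers, no baseline gap and an equal gap at later surveys. The single-survey figures borrow nothing from other surveys.

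**What to change.** In Results, remove the statement that power is sufficient. Report instead the power or detectable difference for the between-arm contrast at the end of the intervention: about 0.41 at 0.44 SD with 64 dyads, or about 0.71 SD detectable with 0.80 power. State the assumed pattern of effect across surveys. If the interaction power is kept, give the gap that it corresponds to (about 1.02 SD).

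In Sampling and Recruitment Plan, name the effect and the surveys behind the 92 dyads and give the matching figure (about 0.55 for a single-survey contrast at 0.44 SD).

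Leave the hypotheses and the midpoint contrast as they are. Data collection has ended, so changing their status now would be a post hoc choice, and the correction does not need it. Read non-significant results at individual surveys in light of the lower power.

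The cost is two revised passages and a less favourable stated figure. Data and model are unchanged.
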